**Fig. 4 Fig4:**
[figure not shown]
Weighted Adverse Outcome Score (WAOS). ICU, intensive care unit; NICU, neonatal intensive care unit [21].

Maternal and perinatal mortality ratios will also separately be evaluated, because these ratios are not independent in the combined mortality proportion. Finally, the ratio of maternal and perinatal mortality per total number of deliveries will be analysed.

### Sample size calculation

Power calculation was carried out as described in both Hussey et al. and Woertman et al. [35–37] First the sample size calculation for a standard randomized clinical trial (RCT) was calculated. To show a reduction in CMP of 20% with an alpha of 0.05 and a power of 80%, a total of 6398 deliveries will be needed for a simple RCT design. The design effect was calculated assuming an intracluster correlation (ICC) of 0.05, a cluster size of 3343 deliveries per year, and seven clusters. Considering the design effect, we will need 2367 deliveries per measurement period. To achieve this number at least 5 weeks for each period will be needed. However, to obtain logistical possibilities, the duration of each step will be 7 weeks with a total study duration of 56 weeks. Statistical significance will be accepted at a two-sided *p*-value < 0.05.

### Statistical analysis

All data will be collected, secured and stored in Mulago hospital. Access to the final trial dataset will be limited to persons who have to perform statistical analyses and to interpret results. The statistical analysis of the stepped wedge design will be analysed in different steps. First of all, differences in patient characteristics (age, parity, gestational age, single/multiple pregnancy, neonatal gender, birth weight) across clusters will be investigated with Kruskal-Wallis for numerical data and with exact chi-square statistics for categorical data. The characteristics that seem to be different across clusters (*p* < 0.05) will enter into the generalized linear mixed effects model (GLMM) for estimation of treatment effect. Here the outcome is the event (i.e. composite mortality rate, including maternal and perinatal mortality) on the individual and we will use a logit link function to model the probability of the event. In the logit scale, the cluster indicator will serve as random effect on the intercept, the selected patient characteristics will enter this model as linear predictors, the period of the stepped wedge is treated as categorical effect, as well as the treatment effect.

In mathematical terms the model can be formulated as follows:
$$ \mathrm{logit}\left[P\left({Y}_{ij}=1|{Z}_i,{\boldsymbol{P}}_{ij},{\boldsymbol{X}}_{ij},{T}_{ij}\right)\right]=\mu +{Z}_i+\sum \limits_{r=1}^R{\alpha}_r{P}_{ij r}+\sum \limits_{s=1}^S{\beta}_s{X}_{ij s}+\gamma {T}_{ij} $$with the logit function given by logit(*x*) = log *x* − log(1 − *x*) and

*Y*_*ij*_: the binary outcome on patient *j* in cluster *i*,

*Z*_*i*_: the random effect of cluster *i*, assumed to be normally distributed $$ {Z}_i\sim N\left(0,{\sigma}_C^2\right) $$, and with $$ {\sigma}_C^2 $$ the between-cluster variance,

***P***_*ij*_: a vector of indicators ***P***_*ij*_ = (*P*_*ij*1_, *P*_*ij*2_, …, *P*_*ijR*_)^*T*^ for patient *j* in cluster *i* that indicate in which period the observation is taken, with $$ {\sum}_{r=1}^R{P}_{ijr}=1 $$ and *R* the number of periods,

***X***_*ij*_: a vector of confounders ***X***_*ij*_ = (*X*_*ij*1_, *X*_*ij*2_, …, *X*_*ijS*_)^*T*^ for patient *j* in cluster *i*, and *S* the number of covariates.

*T*_*ij*_: the treatment indicator for patient *j* in cluster *i*.

*μ*: the overall intercept,

*α*_*r*_: the effect of period *r*

*β*_*s*_: the effect of confounder *X*_*ijs*_

*γ*: the effect of treatment [45].

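### Covariates enter the primary model through a p<0.05 screen across clusters, which checks trained-versus-untrained imbalance only indirectly, ignores prognostic strength and leaves the adjustment set unknown until the data are in

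*Protocol article*

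**What the plan says.** The Statistical analysis section of the protocol article sets out a sequence. First, "differences in patient characteristics (age, parity, gestational age, single/multiple pregnancy, neonatal gender, birth weight) across clusters will be investigated with Kruskal-Wallis" if numerical, and with exact chi-square statistics if categorical. Second, "The characteristics that seem to be different across clusters" at p<0.05 "will enter into the generalized linear mixed effects model (GLMM) for estimation of treatment effect". In that model, "the cluster indicator will serve as random effect on the intercept", and "the period of the stepped wedge is treated as categorical effect, as well as the treatment effect". On functional form, the section says that "the selected patient characteristics will enter this model as linear predictors".

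The article names no covariate that is adjusted for whatever its test result, and no version of the primary model without this selection. Because the article itself fixes the rule, this is not a detail left to a separate analysis plan.

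**The concern.** A covariate deserves a place in a treatment-effect model if it predicts the outcome, and more so if it also differs between the treatment conditions. The screen asks a different question: whether the seven clusters differ from one another. Under Design, all clusters cross from untrained to trained, so cluster membership is not treatment status. The model already carries a cluster effect.

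Three things are at stake:

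- A modest case-mix difference between trained and untrained deliveries can go unadjusted.
- Strong predictors of perinatal death, such as gestational age or birth weight, can be left out because they happen to be balanced across clusters.
- The odds ratio on the logit scale is non-collapsible, so the quantity estimated by γ depends on which covariates the screen admits.

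**Working it through.** The plan gives no figure of its own for how this rule behaves, so the check builds on its design figures.

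**Inputs from the protocol article.** Seven clusters and eight periods of 7 weeks (Fig. 2 caption); 3343 deliveries per cluster per year, ICC 0.05 and 56 weeks in total (Sample size calculation); six candidate characteristics (Statistical analysis).

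**Size of the data.** 7 × 3343 = 23,401 per year, in line with the ward's stated volume of over 23,000. Over the trial, 23,401 × 56/52 ≈ 25,200 deliveries: about 3,600 per cluster and 450 per cluster-period.

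**1. Stable cluster differences hardly reach the treatment estimate at the planned ICC.** I computed generalised least squares weights for the 7 × 8 wedge with a random cluster intercept and categorical periods (a linear approximation to the logit model). At ICC 0.05 the summed weights on a constant shift in each cluster, in roll-out order, are 0.0035, 0.0023, 0.0012, 0, −0.0012, −0.0023 and −0.0035. Take a linear gradient along the roll-out order with SD 1, that is, cluster values 1.5, 1, 0.5, 0, −0.5, −1, −1.5. The covariate balance of the estimate moves by

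2 × (1.5 × 0.0035 + 1 × 0.0023 + 0.5 × 0.0012) ≈ 0.016.

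A shift confined to trained cluster-periods passes through with weight 1.

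**2. What the screen detects of a trained-versus-untrained shift.** The fraction of periods spent trained runs from 7/8 in the first cluster to 1/8 in the last, with SD 0.25. A shift of d SD in all trained deliveries therefore gives the cluster means an SD of 0.25d. The probability of p<0.05 is approximated by a noncentral chi-square with 6 df and noncentrality λ = 7 × 3600 × (0.25d)².

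| Shift d | SD of cluster means | λ | P(flagged) |
|---|---|---|---|
| 0.05 | 0.0125 | 3.94 | 0.27 |
| 0.10 | 0.025 | 15.75 | 0.86 |
| 0.15 | 0.0375 | 35.4 | 0.998 |

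A Kruskal-Wallis simulation at d = 0.1 (400 runs) gave 86.5%.

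**3. Dependence on sample size.** Same formula, λ = N × SD²:

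| SD of cluster means | N = 2,367 | N ≈ 25,200 |
|---|---|---|
| 0.01 | 0.06 | 0.18 |
| 0.02 | 0.09 | 0.65 |
| 0.03 | 0.15 | 0.97 |
| 0.05 | 0.40 | >0.999 |

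N = 2,367 is the plan's requirement for one measurement period and serves only as a smaller comparator.

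**4. Openness of the final model.** Six candidates allow 2⁶ = 64 covariate sets. If no characteristic truly differed and the tests were independent, the chance that at least one enters would be 1 − 0.95⁶ = 0.265.

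**5. Effect on the odds ratio.** Assume a baseline event probability of 0.11 and a covariate with a log odds ratio of 1 per SD; neither is in the protocol. A 20% reduction is then an odds ratio of 0.781 without the covariate (0.088/0.912 divided by 0.11/0.89) and 0.762 with it. With a log odds ratio of 1.5, the adjusted value is 0.737. At an assumed baseline of 0.025 the corresponding values are 0.796 unadjusted, and 0.790 and 0.779 adjusted.

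**The case against.** Several counter-arguments stand and limit the point.

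- **The screen is not blind to the relevant contrast.** A reader might infer that it cannot see trained-versus-untrained imbalance at all. That would be wrong: clusters spend different fractions of the trial trained, so such a shift moves the cluster means, and larger shifts are usually caught. One can construct a 0.1 SD shift that enters only at the chance rate of 5%, but this requires cluster differences that cancel the shift exactly.
- **Absorption by the random intercept is not guaranteed.** It rests on the planning ICC. At ICC 0.001 the SD 1 gradient moves the balance by 0.58 rather than 0.016. All clusters work on one ward, so a low ICC cannot be ruled out, and adjusting for cluster differences would then be worthwhile.
- **The analyst has no free choice.** Candidates, tests, threshold and model are stated beforehand, and the screen never uses the outcome. A reading that covariates could be picked to favour a result has no support in the document.
- **Common time trends are handled.** The categorical period term removes calendar drift shared by all clusters, and the roll-out order is random. What remains is case-mix change aligned with training within clusters, and the article reports none.
- **Over-inclusion does little harm.** With about 25,200 deliveries, an unnecessary coefficient costs little. Neither the 97% nor the 26% is a bias or an error rate for the treatment test.
- **Straight-line terms are not established.** The phrase about linear predictors might be read as forcing log-odds of death to be linear in gestational age and birth weight. It can equally mean terms in the model's linear predictor, and categorical characteristics are among the candidates.

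None of this answers the two remaining points: selection ignores prognostic strength, and the adjustment set is unknown in advance.

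**Conclusion.** The concern holds as a moderate weakness that is cheap to repair. The screen is an indirect check that misses a 0.05 SD trained-versus-untrained shift about 73% of the time (1 − 0.27). It admits cluster differences of no practical size because N is large, and it gives no weight to whether a variable predicts death. The conditional odds ratio reported as the primary result is therefore defined only after the screen has been run. In the illustrations the odds ratio changes modestly, for example from 0.781 to 0.762.

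The detection figures assume about 3,600 deliveries per cluster, equal cluster-period sizes and the chi-square approximation to the rank test. The absorption result assumes ICC 0.05 and a linear approximation. The SD shifts, baseline rates and prognostic strengths are assumptions. The material does not show that the planned analysis is biased or that its type I error is inflated.

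**What to change.** In the Statistical analysis section:

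1. Keep the Kruskal-Wallis and chi-square comparisons across clusters as description only, and remove the p<0.05 entry rule.
2. Name the adjustment set now, on prognostic grounds and whatever the p-values, from the characteristics already listed: for example maternal age, parity, gestational age, single or multiple pregnancy, and birth weight. If neonatal gender is left out, give the reason.
3. Report the model with cluster, period and treatment only alongside the adjusted one, and state which of the two is primary.
4. State how missing or uncertain covariate values are handled. The Discussion itself expects uncertainty in gestational age, and a complete-case fit could drop deaths.

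Flexible terms (categories or splines) for gestational age and birth weight are optional, but saying how the continuous variables are coded would remove the ambiguity noted above.

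The cost is wording plus the missing-data rule. No new variables are needed, and no sample size, power or alpha figure changes.

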A limitation of this most accurate study design in one hospital is the need of fixed teams without contamination during working hours. Due to organizational constraints, such as exam periods and cluster inconsistency, this design may be hard to implement in a low-income country. Therefore pre-post analyses will be performed as well. Additionally, it was logistical impossible to create multidisciplinary fixed teams including midwives, junior house officers, SHOs, gynaecologists, paediatricians, and anaesthesiologist. Team training was set up monodisciplinary, with only first-, second-, and third-year SHOs. This group was chosen as they have a central and coordinating role in providing emergency obstetric care in this hospital, and they have to work in teams during their shift. However, training all obstetric team member would possibly contribute more to reduce maternal and neonatal morbidity and mortality. Another limitation is the selection of only gynaecologists to become local facilitators. They were selected by the head op department based on their clinical and teaching experience. Future studies should include other obstetric team members as facilitators and should include evaluation of personal suitability.

The primary outcome will be a composite of the maternal mortality ratio (MMR) and the perinatal mortality ratio (PMR). While there is a clear definition of the perinatal mortality ratio, issues with routine antenatal care visits and administration difficulties will give uncertainties in gestational age and moment of death. This will maybe influence data collection and interpretation. Improvement of data administration seems to be an important worldwide issue.

The current project fits well within the formulated Sustainable Development Goals agenda to ensure healthy lives and to promote wellbeing for newborns and mothers by specifically increasing the development, training and retention of health workforce in developing countries [4]. If this training program appears to be effective, this training should be implemented in the curriculum of the gynaecology training program in comparable low-income settings.

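### The primary GLMM has no cluster-by-period term, so team-specific change over time would make the standard error of the treatment effect too small

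*Protocol article*

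**What the plan says.** The Statistical analysis section gives the primary model in words and as an equation. It is a logistic mixed model with fixed categorical periods, selected patient characteristics and a treatment indicator. On the random part it says: "In the logit scale, the cluster indicator will serve as random effect on the intercept". In the equation that intercept, normal with one between-cluster variance, is the only random term.

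The Sample size calculation section rests on one correlation: "The design effect was calculated assuming an intracluster correlation (ICC) of 0.05, a cluster size of 3343 deliveries per year, and seven clusters". No separate between-period correlation is given. The caption of Fig. 2 sets seven clusters and eight periods of 7 weeks.

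The Design section expects difficulty in keeping clusters of trainees fixed and free of contamination, and in holding to the 7-week schedule. The Discussion adds: "Due to organizational constraints, such as exam periods and cluster inconsistency, this design may be hard to implement in a low-income country". Both sections respond with an additional pre-post analysis.

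**The concern.** A binomial model has no free residual variance. Once the cluster intercept and the common period effects are in, each cluster-period's event count is assumed to vary only by binomial sampling. If one team's mortality moves between periods for reasons the other teams do not share (changing membership, rota, mix of cases), the model has no term to hold that movement. With about 450 deliveries per cluster-period, binomial error is small enough for modest movement of this kind to matter. The treatment effect is estimated from contrasts between cluster-periods, so its standard error would be understated.

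At stake are the p-value and confidence interval of the primary mortality comparison, and the meaning of the planned 80% power. The model is written out in full, so an analysis plan that follows it would inherit the problem. The pre-post analysis does not change the variance of the primary model.

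**Working it through.** **Inputs from the protocol.** Seven clusters; eight periods; 3343 deliveries per cluster per year; ICC 0.05; 20% relative reduction; two-sided 5%; 80% power; "a total of 6398 deliveries will be needed for a simple RCT design".

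**Assumptions, not in the protocol.** Equal cells. Baseline 10% against 8%, because the baseline is not stated and 6398 implies about 10%. CAC, the between-period correlation divided by the within-period correlation, at 0.95, 0.90 and 0.80.

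**1. Reproduce the plan's figure.** The Woertman design effect with k = 7, one baseline and one measurement per step is

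DE = [1 + ρ(kn + n − 1)] / [1 + ρ(kn/2 + n − 1)] × 3(1 − ρ) / [2(k − 1/k)].

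With ρ = 0.05 and n = 3343, DE = 0.3692, and 6398 × 0.3692 = 2362. With n = 450 it gives 2354. The stated 2367 is reproduced within 1%. The formula has a single ICC, which means CAC = 1.

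**2. Deliveries per cell.** 3343 × 7/52 = 450 per cluster per 7-week period.

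**3. Variance when CAC is below 1.** Take σ² = 0.09 × 0.91 = 0.0819. Cell means in the same cluster have covariance σ²ρ·CAC. Each cell mean has additional variance σ²ρ(1 − CAC) + σ²(1 − ρ)/n. With X holding the period and treatment columns, and V₀ and V the covariance matrices at CAC = 1 and at the true CAC:

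- reported variance: A = (X′V₀⁻¹X)⁻¹
- actual variance: A X′V₀⁻¹ V V₀⁻¹X A
- r = actual SE / reported SE, and type I error = 2[1 − Φ(1.96/r)]

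At ICC 0.05 the reported SE is 0.00619. At CAC 0.95 the actual SE is 0.00913, so r = 1.48, 1.96/1.476 = 1.33, and type I error is 18%. At CAC 0.90 and 0.80, r is 1.83 and 2.39.

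| ICC (proportion scale) | CAC 0.95 | CAC 0.90 | CAC 0.80 |
|---|---|---|---|
| 0.05 | 18% | 29% | 41% |
| 0.01 | 8% | 10% | 15% |
| 0.005 | 6% | 8% | 10% |
| 0.001 | 5% | 5% | 6% |

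At ICC 0.05 and CAC 0.95 the cluster-period SD is √(0.0819 × 0.05 × 0.05) = 0.014, or 1.4 percentage points, against a target difference of about 2 points.

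**4. ICC 0.05 read on the logit scale.** The between-cluster variance is (0.05/0.95) × π²/3 = 0.173. On the proportion scale this is an ICC of roughly 0.173 × 0.0819 = 0.014. Simulation on this scale gave type I error of about 10%, 14–16% and 20–23% at CAC 0.95, 0.90 and 0.80. It returned to about 5–6% with over-dispersion and a t reference.

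**5. Simulation of the protocol's own GLMM** (2,000 trials per scenario, Wald test, ICC on the proportion scale).

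| | CAC 1 | 0.99 | 0.95 | 0.90 | 0.80 |
|---|---|---|---|---|---|
| Type I error, ICC 0.05 | 5.1% | 8.0% | 21.8% | 31.3% | 43.8% |
| Type I error, ICC 0.01 | 5.2% | 5.4% | 8.8% | 10.6% | 16.1% |

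A cell-level analysis that allows cluster-period variance, with t on 41 df, gave 4.2% to 5.7% throughout. At ICC 0.05, keeping the protocol's model and only changing to t on 6 df still rejected 10%, 19% and 31% of the time at CAC 0.95, 0.90 and 0.80 (400 trials each).

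**6. Power.** At 2367 per period (338 per cell) and CAC 1, the SE is 0.00619 × √(450/338) = 0.00714, and Φ(0.02/0.00714 − 1.96) = 80%, as planned. At 450 per cell it is 90%. With the correct variance at ICC 0.05 it falls to 59%, 43% and 28% at CAC 0.95, 0.90 and 0.80; at ICC 0.01 it is 82%, 76% and 65%.

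**The case against.** The model is a standard one and matches the method used for the sample size; nothing is miscalculated. All teams work on one ward and one calendar, so shared shocks go into the period effect, and selected patient characteristics adjust for part of the case mix. The CAC appears nowhere in the protocol. An ICC of 0.05 on the proportion scale is extreme for teams in one hospital: √(0.05 × 0.0819) is a between-team SD of 6.4 points around 9% mortality. All of this stands, and it limits the size of the problem. It does not remove it, because neither the period effect nor the covariates capture change specific to one team.

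Three stronger readings are tempting, and the document does not support them.

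- **That a false claim of benefit is likely.** The largest rates hold only for ICC 0.05 on the proportion scale with CAC well below 1. The protocol states neither the scale nor a CAC.
- **That omitting a small-sample correction for seven clusters is itself an error.** With CAC 1 the uncorrected GLMM held 5.1% and 5.2% at ICC 0.05 and 0.01. It reached 8.3% only at ICC 0.001. A reference distribution is also something an analysis plan normally supplies.
- **That the protocol itself predicts decaying correlation.** Its remarks on exam periods and cluster inconsistency concern feasibility and contamination. They make team-specific variation plausible and say nothing about its size.

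**Conclusion.** The point holds as a should-fix. The stated model assumes that correlation within a cluster does not weaken over time, and nothing in the plan protects the primary standard error if it does. The direction of the bias is certain once team-specific variation exists. Its size depends on an unstated CAC and on the ICC and its scale. Over the assumed CAC range of 0.95 to 0.80, type I error runs from 6–10% at ICC 0.005, through about 10–23% at ICC 0.05 on the logit scale, to 18–41% at ICC 0.05 on the proportion scale. Inflation from this source is slight at an ICC near 0.001, or at CAC 0.99 with ICC 0.01. The planned power carries the same assumption, so it is an upper figure rather than a safe one.

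**What to change.** Add a random cluster-by-period intercept, with its own variance, to the primary GLMM equation. Accompany it with either a small-sample t reference or a randomisation test over the 7! = 5,040 possible training orders. A small-sample reference without the extra variance term would not be enough. Beside the current power figure, report power over a stated CAC range, for example 0.80 to 0.95, and say on which scale the ICC of 0.05 is meant.

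The cost is one extra variance term and, if the randomisation test is chosen, the programming for it. Intervals become wider and the power figure less favourable. No extra deliveries are needed.

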### Ethical considerations

Ethical approval was obtained from both the Mulago Research and Ethics Committee (Protocol MREC: 674), and the Uganda National Council for Science and Technology (UNCST, SS 3927). Written informed consent to participants in this study was obtained at the beginning of the first training day.

## Discussion

In the last decades numerous evaluation studies on the effectiveness of simulation training in obstetric emergencies have been published, with increasing evidence that it is associated with improvement in clinical outcomes [13–32]. However, the results are not entirely consistent. The need for continued research in a wide variety of clinical settings to establish what works, where and why was recommended [14, 33]. Therefore we propose to use a randomized controlled trial design in settings where emergency obstetric simulation-based training is not yet widely established.

This stepped wedge cluster randomized trial will investigate the effect of a monodisciplinary simulation-based obstetric training focusing on both medical technical skills and crew resource management skills in a low-income country, on patient outcome at one of the largest labour wards worldwide. In this study, also other non-patient outcome measures will be included. We hypothesize that simulation-based obstetric training in a low-income country is acceptable and feasible for trainers and trainees, improves knowledge, skills, team performance and professional practice, and improves maternal and neonatal morbidity/mortality rates. Different from previous studies, we will use a robust study design which will allow us to better understand the training effects.

A limitation of this most accurate study design in one hospital is the need of fixed teams without contamination during working hours. Due to organizational constraints, such as exam periods and cluster inconsistency, this design may be hard to implement in a low-income country. Therefore pre-post analyses will be performed as well. Additionally, it was logistical impossible to create multidisciplinary fixed teams including midwives, junior house officers, SHOs, gynaecologists, paediatricians, and anaesthesiologist. Team training was set up monodisciplinary, with only first-, second-, and third-year SHOs. This group was chosen as they have a central and coordinating role in providing emergency obstetric care in this hospital, and they have to work in teams during their shift. However, training all obstetric team member would possibly contribute more to reduce maternal and neonatal morbidity and mortality. Another limitation is the selection of only gynaecologists to become local facilitators. They were selected by the head op department based on their clinical and teaching experience. Future studies should include other obstetric team members as facilitators and should include evaluation of personal suitability.

The primary outcome will be a composite of the maternal mortality ratio (MMR) and the perinatal mortality ratio (PMR). While there is a clear definition of the perinatal mortality ratio, issues with routine antenatal care visits and administration difficulties will give uncertainties in gestational age and moment of death. This will maybe influence data collection and interpretation. Improvement of data administration seems to be an important worldwide issue.

The current project fits well within the formulated Sustainable Development Goals agenda to ensure healthy lives and to promote wellbeing for newborns and mothers by specifically increasing the development, training and retention of health workforce in developing countries [4]. If this training program appears to be effective, this training should be implemented in the curriculum of the gynaecology training program in comparable low-income settings.

